**Sample size calculation and Statistical Analysis:**

All patients will undergo a 3-month run in phase, during which they will be on detemir and aspart only, with no added metformin or placebo. (Please see a detailed explanation of the run-in phase under Trial Design above). At the end of the run-in period,patients will be assigned to one of the two treatment groups (placebo or metformin) using a random number generation process. Placebo and metformin will be offered in similar form, to ensure participants are blinded to their assignment. Group assignment will be established by a research pharmacist with no direct participation in the study; and principal investigator will not be informed of what group each individual is assigned to.

The primary outcome chosen to measure the impact of metformin on the management of “double diabetes” children is their level of glycosylated hemoglobin (Hb A1c, measured as a %). The secondary outcomes are: a) blood pressure (mmHg), b) waist circumference (cm), c) body mass index (BMI, kg/m2), d) lipid profile (LDL and HDL cholesterol and triglycerides (mg/dL)), e) ), leptin (ng/dL), and f) 25-hydroxyvitamin D (ng/mL), g) adiponectin (µg/mL ), and total daily dose of insulin.

All outcomes will be measured on an ongoing basis, at the beginning of the trial, and then at 3 months intervals during the entire study period. The intervention arm of the study will last 9 months. **Sample size calculations** are based on the simple comparison of paired means. Using a confidence level of 95% (Z (1-α/2) = 1.96 for a two-tailed test) and a statistical power of 80% (Z (1-β) = 0.84), calculated group sizes are 29 individuals for each arm of the trial. This number is based on the assumptions that 1) supplementing the treat-to-target protocol with metformin will decrease the Hb A1c level by at least 1.5 percent units, and 2) the standard deviation for Hb A1c levels in obese adolescents is estimated to be 2. Because of the duration of the study, and the possibility of loss to follow-up, a 25% attrition allowance has been made on the ‘n’ of 58, bringing the total number of participants to 74. This is a conservative approach to the sample size calculation, because the repeated measurements will, by construction, improve the power of the study, improving its ability to capture outcomes with more variability than expected.

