**Subject Replacement:** To ensure adequate sample size to reach significance according to our power calculations, we will oversample by 25% for each arm of the study. This will enable adequate numbers despite predicted study attrition.

**Statistical analyses** will be conducted so as to capture both the absolute changes in serum values for the proposed outcomes, as well as “time-to-event” information allowing us to compare the 2 groups with maximum efficiency.

1) **H1A**: Metformin supplementation of treat-to-target insulin regimen of diabetes care will have an influence on levels of HbA1c over time.

Mean levels of HbA1c will be computed at each time point, applying arcsine transformation to approximate Normality. 95% Confidence Intervals (95% CI) will be constructed around these estimates. All results will be graphed for visual appreciation of possible trends. Consecutive HbA1c levels for patients with and without metformin will be compared using repeated-measures Analysis of variance (ANOVA). Analyses of Covariance will be modeled to account for possible confounding due to gender and age. Similar analyses will be applied to the FPG levels, using the logarithmic transformation instead.

2) **H1B**: Patients randomized to adjunctive metformin therapy will achieve a greater reduction in HbA1c and fasting plasma glucose than those on placebo.

Adjunctive metformin and placebo groups will also be compared using both a logistic model and an actuarial survival model for “time-to-event”, where the event of interest is the decrease of the HbA1c level to 8% or less, as the biological cutoff below which serum glucose levels are considered stabilized. Similar analyses will be applied to FPG levels.

3) **H1C**: Metformin supplementation of treat-to-target regimen of diabetes care will have a measurable influence on blood pressure, waist circumference, body mass index, lipid profile, leptin, adiponectin, and 25-hydroxyvitamin D.

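### The HbA1c comparison names no deciding contrast or test, leaves month-0 HbA1c out of the covariates, and uses an arcsine scale that does not match the 1.5-point planning difference

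*Protocol*

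**What the plan says.** Everything relevant is in Protocol section 4c, in the sample size text and the statistical analyses listed after it.

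- Sizing: HbA1c level is the primary outcome. "calculated group sizes are 29 individuals for each arm of the trial", assuming that "supplementing the treat-to-target protocol with metformin will decrease the Hb A1c level by at least 1.5 percent units" and that "the standard deviation for Hb A1c levels in obese adolescents is estimated to be 2", with 80% power and a two-sided 5% level. An attrition allowance of 25% brings the total to 74. The text adds that repeated measurement necessarily improves power, and so calls the calculation conservative.
- H1A: mean HbA1c at each visit is computed "applying arcsine transformation to approximate Normality". Then "Consecutive HbA1c levels for patients with and without metformin will be compared using repeated-measures Analysis of variance (ANOVA"). Covariates: "Analyses of Covariance will be modeled to account for possible confounding due to gender and age".
- H1B: the arms "will also be compared using both a logistic model and an actuarial survival model" for reaching HbA1c of 8% or less. Fasting plasma glucose gets similar analyses under both hypotheses.

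HbA1c is drawn at months 0, 3, 6 and 9 (section 4a and the descriptions of Visits III to VI). No contrast, time point, order of tests or division of alpha is attached to these analyses.

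**The concern.** The protocol does not leave the method open. It fixes a transformation, a model family and a covariate list, and each choice sits badly with the sizing.

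- A repeated-measures ANOVA over four visits yields more than one F-test. Month 0 precedes the oral agent, so the expected arm difference there is zero. A group effect that averages it in is diluted.
- Month-0 HbA1c would be expected to predict later HbA1c. It is available for everyone at no cost, yet it is not used as a covariate.
- The arcsine transformation is meant for binomial proportions. HbA1c is a continuous assay value that happens to be expressed in percent.
- Three analyses address one HbA1c question, and none is named as deciding.

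At stake are whether the trial has the power it claims, whether its main result is in HbA1c points, and whether the deciding analysis is fixed before the data are seen.

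**Working it through.** **The plan's own figure.** With alpha 0.05 two-sided, power 80%, difference 1.5 and SD 2, n per arm = 2 × (1.96 + 0.84)² × 2² / 1.5² = 27.9, or 28. The t-test version gives 28.9, or 29, which matches. The text labels this a comparison of paired means, but a paired formula would give 13.9. The 29 is therefore an unadjusted comparison of two independent means.

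**Inputs for the power check.** SD 2 at each visit; difference 0 at month 0 and 1.5 at months 3, 6 and 9; n = 74 × 0.75 / 2 = 27.75 per arm. The protocol gives no between-visit correlation r, so an equal correlation of 0.5 to 0.8 between all visits is assumed.

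For the z-type contrasts, power = Φ(difference / √(2V/n) − 1.96):

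- Month 9, unadjusted: V = 4, SE = 0.537, power = Φ(0.834) = 79.8%.
- Group effect over months 0-9: difference = 0.75 × 1.5 = 1.125 and V = 4(1 + 3r)/4. At r = 0.5, SE = 0.424 and power = Φ(0.690).
- Group effect over months 3-9: difference = 1.5 and V = 4(1 + 2r)/3. At r = 0.5, SE = 0.438 and power = Φ(1.461).
- Month-9 ANCOVA on month-0 HbA1c: difference = 1.5 and V = 4(1 − r²). At r = 0.5, SE = 0.465 and power = Φ(1.266).

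For group-by-time, the noncentral F has noncentrality (n/2) × Σ(d − mean d)² / [4(1 − r)]. Here Σ = 1.125² + 3 × 0.375² = 1.6875. At r = 0.5 this gives 13.875 × 1.6875 / 2 = 11.7, on 3 and 160.5 degrees of freedom.

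| Contrast | r = 0.5 | 0.6 | 0.7 | 0.8 |
|---|---|---|---|---|
| Group effect, months 0-9 | 76% | 71% | 66% | 62% |
| Group-by-time | 82% | 90% | 97% | over 99% |
| Group effect, months 3-9 | 93% | 90% | 88% | 85% |
| Month-9 ANCOVA | 90% | 94% | 97% | over 99% |

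The shortfall in the top row depends on r. At 29 per arm, that contrast has 82% power at r = 0.4 and 87% at r = 0.3.

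**Arcsine scale.** The usual arcsine square-root form is assumed.

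- A 1.5-point fall from 9.5% is arcsin√0.095 − arcsin√0.080 = 0.0266.
- The same fall from 12% is arcsin√0.120 − arcsin√0.105 = 0.0237.

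The same fall in points is thus a different effect on the analysis scale, depending on where the patient starts. In simulation (3,000 trials per scenario, 29 per arm, r = 0.5 and 0.7) the transformation changed power by under 3 points in every comparison.

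**Several tests.** Three independent tests at 5% give 1 − 0.95³ = 14.3%. The same simulation was run under no arm difference, assuming a month-0 mean of 9.5 and a common fall of 0.8. The chance that at least one of ANOVA, logistic and log-rank has p < 0.05 was 14.3% (r = 0.5) and 13.1% (r = 0.7) using group-by-time, and 12.8% and 10.0% using the months 0-9 group effect.

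**Missing visits.** If 25% of 74 are lost, 55.5 remain, below the 58 required. In its classical form, repeated-measures ANOVA uses only participants with every visit.

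**The case against.** The strongest reply is that H1A concerns HbA1c across time, so the natural test is group-by-time. That test already uses within-patient change. On the same assumptions it has 82% to over 99% power, never below plan, and it matches month-9 ANCOVA from r = 0.7. This stands. A reader might infer that the plan flatly costs power, but the document does not support that. The loss belongs to one contrast that the protocol neither selects nor rules out.

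Four other inferences also go too far:

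- **That only completers will be analysed.** The protocol does not say so. Dropping incomplete participants is a property of the classical method, and missing-data rules may be in an analysis plan not shown.
- **That the false-positive rate is inflated.** The 10-14% applies only if success on any of the three tests may be claimed. HbA1c is the single primary outcome, the ANOVA comes first, and the other two tests fall under a separate hypothesis. An analysis plan could set the order.
- **That arcsine loses power, or that no result can be given in points.** It does not lose power, and the protocol also intends to capture absolute changes. The narrower complaint stands: the named comparison is on a scale other than the one used for sizing.
- **That omitting the entry route (type 1 or type 2) is an error.** Adding it is a preference; the omission does not bias a randomised comparison. Nor is there anything wrong with keeping sex and age.

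It is also an inference that the ANOVA is primary, since the protocol never labels it so.

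**Conclusion.** The concern holds in limited form. The protocol fixes a method but not the contrast or test that decides. It omits month-0 HbA1c as a covariate and puts the main comparison on a scale that does not return the 1.5 points used for sizing.

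On the stated assumptions, power at r = 0.8 runs from 62% to over 99% according to a choice the document does not make. The low end contradicts the statement that repeated measurement necessarily improves power: a group effect that averages in month 0 does worse than the unadjusted month-9 comparison (79.8%) throughout the assumed range of r. The size rests on r of 0.5 to 0.8, equal correlation between visits and a constant effect from month 3. None of these is given in the protocol. The false-positive and missing-visit consequences are conditional, as set out above.

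**What to change.** Name one primary test: the between-arm difference in untransformed HbA1c, in percentage points, at month 9. Take it from a mixed model for repeated measures on months 3, 6 and 9 with month-0 HbA1c as covariate. Sex and age may stay. Include all randomised participants with any post-baseline HbA1c value. Drop the arcsine transformation, and label the logistic, survival and fasting plasma glucose analyses supportive.

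This changes analysis wording only and needs no new data. The cost is that the logistic and survival analyses can no longer carry the primary claim. Month 9 is also a choice: the general hypothesis speaks of more rapid improvement, so the investigators should confirm that the end-of-treatment difference is the claim they want.

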**Table 3. Supplemental Insulin Dose Adjustment Plan**

| Prior meal Blood Glucose levels (mg/dL) | Current meal blood glucose level (mg/dL) | Supplemental Insulin dose (SID) |
| --- | --- | --- |
| greater than 130 | 80-130 | Interpretation: correct SID  Instruction: nothing to do |
| greater than 130 | less than 80 | Interpretation: SID is too high  Instruction: increase sensitivity factor by 10 |
| greater than 130 | greater than 130 | Interpretation: SID is too small  Instruction: decrease sensitivity factor by 10 |

**C. Basal Insulin adjustment plan:** Basal detemir injection will be given consistently at bedtime once a day. Subjects will titrate their long-acting insulin analog (detemir) dose every third day, to achieve a fasting plasma glucose of 90-120 mg/dL using the algorithm shown in Table 2 below. We will aim to maintain participants on a total daily **basal** insulin dose of 0.3-0.8 U/kg/day or higher if necessary, given once daily at bedtime. This will ensure relative normal inter-prandial glycemia and the achievement of our HbA1c targets.

**D. Metformin or Placebo:** All participants will be provided with a 3 month supply of metformin or placebo at baseline, +3, and +6mo. Subjects will be advised to start at one capsule daily for 2 weeks, and then increase to 2 capsules once daily for the remainder of the study duration.

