**Assessments for Efficacy**

1. **Laboratory assessments**: Fasting serum samples will be drawn at baseline and every 3 monthly for the following analytes, lipid panel, leptin, adiponectin, and 25-hydroxyvitamin D. All samples will be spun in a centrifuge and the serum stored at -70 degrees in a freezer at the Division of Endocrinology, Department of Pediatrics, University of Massachusetts Medical School. Whole blood samples will be collected for HbA1c estimation. At the end of the study, all samples will be assayed simultaneously by the Umass Memorial Hospital Biochemistry laboratory. HbA1c, the primary efficacy parameter, will be assayed by the HPLC method. Its inter-assay variability is <1.5%, and intra-assay variability is <2.5%, with a normal range of 4.4.-6.0%. Lipid profile will be assayed by the Enzymatic method; leptin by Human Leptin ELISA kits developed by LINCOplex (Linco Research, St Louis, MO) (sensitivity 0.01 ng/mL, interassay coefficient of variation 5%; adiponectin by Human Adiponectin ELISA kits developed by B-Bridge International (San Jose, CA) (lower limit 0.02 ng/ml; interassay coefficient of variation 3.2%); and 25-hydroxyvitamin D by chemiluminescence assay. All remaining specimens will be disposed of 5 years after the study.
2. **Body mass index**: Using a wall-mounted stadiometer for height measurement, and an electronic scale for body weight measurement, these anthropometic measurements will be obtained at -3, 0, +3, +6 and +9 months. Measurements will be taken in triplicates and the average taken.
3. **Insulin dosing**: All participants will be on basal-bolus insulin regimen. Weekly weight-adjusted total daily doses of insulin will be collected on all participants to identify changes in insulin requirements during the study.

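### FPG levels are read as evidence that metformin works although both arms are titrated to the same FPG target, and insulin dose, a listed secondary outcome, has no comparison in H1A to H1D

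*Protocol*

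**What the plan says.** All places are in the Protocol.

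- **Sample size calculation and Statistical Analysis, H1B:** "Patients randomized to adjunctive metformin therapy will achieve a greater reduction in HbA1c and fasting plasma glucose than those on placebo". The logistic and time-to-event models are built on an HbA1c of 8% or less, and then "Similar analyses will be applied to FPG levels". No FPG event is given.
- **Same section, H1A:** HbA1c is compared by repeated-measures ANOVA, and "Similar analyses will be applied to the FPG levels, using the logarithmic transformation instead".
- **Visit III, Procedure, item C (basal insulin):** "Subjects will titrate their long-acting insulin analog (detemir) dose every third day, to achieve a fasting plasma glucose of 90-120 mg/dL". The detemir titration table (the second table numbered 2) adds 2 units when the three-day average is above 120, removes 2 below 90 and makes no change between. Item A places all participants on the treat-to-target regimen, with metformin or placebo added.
- **Sample size section, outcome list:** the secondary outcomes end with "and total daily dose of insulin". FPG is not in that list.
- **Assessments for Efficacy, Insulin dosing:** "Weekly weight-adjusted total daily doses of insulin will be collected on all participants to identify changes in insulin requirements during the study".
- **H1C:** metformin "will have a measurable influence on blood pressure, waist circumference, body mass index, lipid profile, leptin, adiponectin, and 25-hydroxyvitamin D". Insulin dose is absent. It is also absent from H1A and H1B (HbA1c and FPG), from H1D (HbA1c only) and from the Secondary Aims.

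**The concern.** FPG is the quantity that the regimen controls. When a rule moves basal insulin until FPG lies in a fixed band, and the rule is the same in both arms, an added glucose-lowering drug mainly changes how much insulin is needed to reach the band. The Protocol's own risk section describes this feedback: basal insulin will follow the prevailing glycaemia once metformin is added.

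The hypotheses therefore look for efficacy in late FPG levels, where successful titration removes it, and assign no comparison to the dose, where it should then be visible. A null FPG result would say little about metformin. Equal HbA1c reached with less insulin would appear in no planned comparison.

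**Working it through.** **1. The plan's own figure.** The stated 29 per arm is for HbA1c (difference 1.5, SD 2, two-sided 5%, 80% power): n = 2 × (1.96 + 0.84)² × 2² / 1.5² = 27.9, so 28; the t-test version gives 28.9, so 29. It reproduces and is not in dispute. It serves below only as the group size.

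**2. Room for the algorithm to act.** One step of 2 units every third day allows 90/3 = 30 steps (60 units) by month 3 and 270/3 = 90 steps (180 units) by month 9.

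**3. Expected end state.** Let metformin lower FPG by m at a fixed insulin dose, and one unit of detemir lower it by s. If both arms reach the same FPG, the dose difference is m/s. The Protocol gives neither value. Assuming m = 20 mg/dL, s = 1, 2, 3 or 4 mg/dL per unit gives 20, 10, 6.7 or 5 fewer units on metformin.

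**4. Simulation of the ±2 unit rule.** Assumptions, none of them from the Protocol: starting FPG 200 mg/dL (SD 40), reading noise SD 30 (so 30/√3 = 17.3 for a three-day mean), m = 20, titration from month 0, 20,000 subjects per arm. Entries are metformin minus placebo.

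| Adjustments made | s (mg/dL per unit) | FPG, month 3 | FPG, month 6 | FPG, month 9 | Detemir units, month 9 |
|---|---|---|---|---|---|
| all | 1 | -13.1 | -4.5 | -0.8 | -18.7 |
| all | 2 | -4.9 | -0.1 | -0.1 | -10.0 |
| all | 4 | 0.0 | 0.0 | -0.1 | -5.0 |
| half | 1 | -17.8 | -13.9 | -9.2 | -11.2 |
| half | 2 | -13.8 | -5.0 | -1.0 | -9.7 |
| half | 4 | -5.1 | -0.2 | 0.0 | -5.0 |
| 10% | 1 | -19.5 | -19.1 | -18.6 | -1.4 |
| 10% | 2 | -18.8 | -17.7 | -16.4 | -1.6 |
| 10% | 4 | -17.8 | -14.7 | -11.1 | -2.2 |

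A variant with starting SD 35, s = 1, 2, 3 and full adherence gives FPG differences of 1-14 mg/dL at month 3 and of 0.7, 0.0 and 0.0 at day 273, with 19.0, 9.8 and 6.8 fewer units.

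**5. What the tests could see at 29 per arm.** Power = Φ(δ / (SD × √(2/29)) − 1.96), counting only the tail in the expected direction.

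- FPG, with an assumed SD of 40-60: an untitrated difference of 20 mg/dL has 48-25% power; a difference shrunk to 5 has 7-5%.
- Within the variant simulation, month 9 power is about 5% for FPG level and 56-59% for detemir dose.
- Total insulin dose: one trial cited in the Background reports changes of -0.14 and 0.02, a difference of 0.16 (units not printed; U/kg/day assumed). Power is 98%, 86%, 53% and 33% at assumed SDs of 0.15, 0.2, 0.3 and 0.4.

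**6. Time to target.** In the variant simulation, take the event as the first three-day mean FPG of 120 mg/dL or less, read from the glucometer downloads (both are assumptions). Median days, placebo against metformin, are about 93 against 63-66, 54 against 39, and 39 against 30 for s = 1, 2 and 3. Log-rank power at 29 per arm is about 45-48%.

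**The case against.** A reader might infer that the whole FPG part of H1B must come out null whether or not metformin works, and that its analyses should be deleted. The documents do not support that, for three reasons.

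- The stated Hypothesis is about speed: glycaemic control improving sooner with metformin. If both arms head for one target, which arm gets there first is a sensible question. Step 6 shows that time to target keeps usable power under the same assumptions that flatten the late levels.
- The repeated-measures analysis also uses month 3, where up to 14 mg/dL can remain with full adherence.
- Full adherence is doubtful. Subjects are enrolled for HbA1c above 8%, and the compliance rule asks for 6 downloads a month, against about 30/3 = 10 on an every-third-day schedule. With 10% of the adjustments made, 11-19 mg/dL persists at month 9.

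A reader might also say that insulin dose has been left out of the trial, or that the effect is certain to appear there. Neither holds. Dose is a named secondary outcome with weekly, weight-adjusted data. Of the two placebo-controlled trials cited in the Background, one found a dose reduction and the other no significant difference.

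It can be said that a model for one secondary outcome belongs in the statistical analysis plan. That is fair for the model. It does not settle the point, because the Protocol itself fixes FPG as efficacy evidence and lists the H1C outcomes without dose.

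Finally, HbA1c is primary and FPG is not in the outcome list, so no primary conclusion rests on FPG. That stands, and it limits the weight of the point.

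**Conclusion.** The point holds for FPG levels, late ones above all, and for the missing dose comparison. Both arms share one FPG target, FPG levels are tested as efficacy under H1A and H1B, and total daily insulin dose is in no hypothesis or described analysis.

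The size depends on adherence and on values that the Protocol does not give. With m = 20 mg/dL and s = 1-3 mg/dL per unit, full adherence leaves an FPG difference of about 1-14 mg/dL at month 3 and 0-1 at month 9, with about 7-20 fewer units of detemir at month 9. With half of the adjustments made, up to 9 mg/dL remains at month 9, with about 7-12 fewer units. The 20-unit end belongs to the weakest assumed insulin response.

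The illustration starts titration at month 0, as Visit III states. The risk section instead has the regimen begin in the run-in, and those passages need to be reconciled.

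HbA1c is open to the same attenuation, less directly because basal insulin is titrated on FPG. That is a reason to read it with dose; it does not invalidate the primary comparison. The change should be made, but the primary analysis does not depend on it.

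**What to change.** 1. Add weight-adjusted total daily insulin dose to H1C as a named between-arm comparison, using the same repeated-measures model with adjustment for the baseline dose.
2. In H1A and H1B, state that late FPG levels check whether titration worked alike in both arms, and are read together with dose and not as stand-alone evidence of efficacy.
3. State that HbA1c is also read with dose: lower HbA1c is a glycaemic benefit, and equal HbA1c at a lower dose is insulin-sparing, not absence of effect.
4. Keep the FPG time-to-event analysis as a supportive test of the speed hypothesis. Define its event in FPG terms, because the 8% cutoff is an HbA1c value, and name the readings that supply it (downloads or three-monthly visits). Give any FPG logistic model the same definition.

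The cost is wording, one more secondary comparison and a less prominent FPG hypothesis. The dose data are already collected, and no titration rule changes.

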**4. DETAILED DESCRIPTION OF RESEARCH PLAN (especially as it affects the subject)**

1. Include a schematic representation of what the research will entail (e.g. a table with the number of visits and what will happen at each visit or flow diagram of subject’s involvement over time).

Table 1. Schematic Representation of the Study Protocol for Trial of optimized Insulin-Metformin Therapy

| Procedure | Visit I  (-3mo): Start of Run-in period +  screening  Duration: 1hr | Visit II (-2 mo)  Run-in period+ | Visit III (month 0)  Baseline study visit: Duration 1hr | Visit IV (month +3)  Interim study visit:  Duration 30 min | Visit V (month +6)  Interim study visit;  Duration 30 min | Visit VI  (month +9)  Study conclusion  Duration:1hr |
| --- | --- | --- | --- | --- | --- | --- |
| History and Physical Exam | X | X | X | X | X | X |
| Nutrition Counseling |  | X | X | X | X |  |
| Instructions on treat-to-target regimen | X | X | X | X | X |  |
| Research Blood draw |  |  | X | X | X | X |
| Urine collection | X |  |  |  |  | X |
| Screening labs  (part of research lab draw) | X |  |  |  |  |  |
| Run in phase | X | X |  |  |  |  |
| Implementation of Treat-to-target regimen | X | X | X | X | X |  |
| Metformin/Placebo |  |  | X | X | X |  |
| Review of blood glucose data and insulin dose adjustments | X | X | X | X | X | X |

Trial design:

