**Inclusion criteria:**

1. **General inclusion criteria**
2. Ten to 18 years of age.
3. Pubertal (Tanner stages 2-5, by examination).
4. Hemoglobin A1c level of > 8.0% in the 6 months prior to enrollment.
5. All subjects must have access to a computer.
6. **Specific inclusion criteria: [Subjects could have either #1, or #2].**
7. Subjects with clinical and biochemical features of T2DM of > 6mo duration who also have positive T1DM antibodies
   1. Clinical features: acanthosis nigricans, BMI >85%
   2. Biochemical: evidence of insulin resistance at diagnosis
      1. fasting insulin >27 uIU/mL(normal range 6-27) at a fasting blood glucose of ≥ 126 mg/dL, or
      2. fasting c-peptide level of > 7.1 ng/mL (normal range 0.9 – 7.1), or
      3. Homeostasis model of insulin resistance of >3.16
8. Patients with T1DM of > one yr duration with BMI >85%
   1. Presentation with ketoacidosis at diagnosis
   2. C-peptide <0.9 ng/mL (normal range 0.9 – 7.1),or (insulin < 6 uIU/mL) (NR 6-27) at diagnosis (when blood glucose is ≥ 126 mg/dL)
   3. Can be antibody positive or negative
   4. Increased insulin requirement (>2 Units/kg/day)

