Mean values for each one of these outcomes will be computed at each time point, applying appropriate transformations where needed to approximate Normality. 95% CIs will be constructed around these estimates. All results will be graphed for visual appreciation of possible trends. Consecutive measurements for patients with and without metformin will be compared using repeated-measures Analysis of variance (ANOVA). Analyses of Covariance will be modeled to account for possible confounding due to gender and age. Non-parametric equivalent of statistical tests will be used where necessary.

4) **H1D**: Transition from standard insulin treatment to treat-to-target regimen will provide better diabetes care for all patients. (Please see Table 2 below for a detailed explanation of the protocol for patient-directed forced-titration regimen).

Mean A1c levels at the beginning (-3mo) and at the end (0 mo) of the run-in period in all patients will be compared to subsequent mean A1c levels in the placebo group, using repeated measures ANOVA. Necessary adjustments for possible confounders will be carried out as described above.

d. Does the study involve randomization?

| YesX |  | No |  |
| --- | --- | --- | --- |

**If yes**, please describe process.

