**1. VISIT I: START OF THE RUN-IN PERIOD AND SCREENING VISIT AT -3 MO**

*History:* To ensure eligibility for the study, we will take a detailed history of subject’s medical condition. This history will focus on patient’s current medical diagnosis, past medical and birth history, social history. We will document any family history of type 1 or type 2 diabetes, obesity, and related comorbidities. We will also document subject’s medications, supplements, diet and exercise plan.

*Physical Examination:* All participants will undergo a detailed physical examination at baseline, and at 3 month intervals throughout the duration of the study. The aims of the physical examination will be (1) to rule out medical conditions that could present with obesity, such as Cushing’s syndrome, severe hypothyroidism, and Prader Willi syndrome; (2) to identify complications of diabetes; (3) to identify dermatologic features associated with insulin resistance, such as acanthosis nigricans, and skin tags; (4) to document appropriate Tanner stages in all participants.

*Screening Laboratory Test:* All participants will undergo a screening study consisting of serum creatinine, liver function tests, thyroid function tests, and celiac antibody panel. Subjects with abnormal liver or kidney function tests will not be enrolled in the study. Subjects with abnormal thyroid function test will be treated and will be enrolled when euthyroid. Subjects with abnormal celiac antibody panel will be enrolled after a consultation with a gastroenterologist.

*Urine Sample:* A spot urine sample will be collected for microalbumin and creatinine at baseline. Urine pregnancy test will be obtained on all female participants and will be repeated at baseline, +3mo, and + 6mo.

*Run-in phase:* All participants will be transitioned to detemir and aspart, without instituting treat-to-target regimen, or adding metformin or placebo. (Please see a detailed explanation of the run-in phase under Trial Design above).

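### H1D needs a month -3 HbA1c that no visit schedules, sets all patients before against placebo patients after in a repeated-measures ANOVA, and words an uncontrolled change as better care for all

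*Protocol*

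**What the plan says.** All places are in the protocol.

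- **Hypothesis.** Under Sample size calculation and Statistical Analysis, H1D reads: "Transition from standard insulin treatment to treat-to-target regimen will provide better diabetes care for all patients".
- **Analysis.** The before values are the HbA1c means from months -3 and 0. The protocol says that these "in all patients will be compared to subsequent mean A1c levels in the placebo group, using repeated measures ANOVA".
- **Aim served.** Secondary Aim 1 is to measure HbA1c changes as patients move from standard to treat-to-target insulin. The section on long-term benefits promises to compare HbA1c changes during standard therapy with those during treat-to-target.
- **Laboratory schedule.** Visit I (month -3) has "a screening study consisting of serum creatinine, liver function tests, thyroid function tests, and celiac antibody panel". In Table 1 the row "Research Blood draw" is marked at Visits III to VI only. The visit descriptions first draw HbA1c at month 0 and redraw it at months 3, 6 and 9. Height and weight, by contrast, are listed at month -3 under Assessments for Efficacy.
- **Entry.** Subjects qualify on "Hemoglobin A1c level of > 8.0% in the 6 months prior to enrollment".
- **Treatment.** After the run-in both arms receive treat-to-target insulin, with metformin or placebo.

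**The concern.** The change on standard insulin is month 0 minus month -3. If no HbA1c is drawn at month -3, the comparison promised for Secondary Aim 1 lacks one of its inputs. The likely stopgap is the eligibility value, which may be up to six months old and was itself the basis of selection.

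The before and after sets are also different groups of people. Repeated-measures ANOVA works within subjects, yet metformin subjects supply before values and no after values. The protocol does not say what happens to them.

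Finally, every subject moves to treat-to-target at the same point, so time and any other change at month 0 are mixed with the regimen. The hypothesis is nevertheless worded as better care for all patients.

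**Working it through.** **1. Is a month -3 HbA1c scheduled?**

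| Source | Month -3 | Months 0, 3, 6, 9 |
| --- | --- | --- |
| H1D analysis | HbA1c needed | HbA1c needed |
| Table 1, research blood draw | not marked | marked |
| Visit I screening laboratory test | creatinine, liver, thyroid, celiac | not applicable |
| Visit descriptions | no HbA1c | HbA1c drawn |

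Blood is drawn at Visit I, since Table 1 marks screening labs there, but HbA1c is not among the tests.

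**2. Sample size.** H1D has no figure of its own, so I use the protocol's. With a difference of 1.5, SD 2, z = 1.96 and 0.84:
- 2 × (2 × 2.80 / 1.5)² = 27.9, so 28 per arm. The t-based version gives 28.9, so 29, as stated.
- 29 × 1.25 = 36.25, so 37 per arm and 74 in total, as stated.
- After 25% loss, 37 × 0.75 = 27.75. I take n = 28 per arm.

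**3. Cost of mixing the arms.** Take one before and one after time point, SD = 2 and within-subject correlation r. The protocol gives no r, so it is assumed. All 2n randomized subjects have a before value; n placebo subjects have an after value.
- As written, placebo after minus all-patient before: SE = SD × √((1.5 − r)/n)
- Placebo subjects against their own before values: SE = SD × √((2 − 2r)/n)
- Likelihood-based mixed model on the data H1D names: SE = SD × √((1 − r)(1.5 + 0.5r)/n)

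At r = 0.6:
- as written: 2 × √(0.9/28) = 0.36
- placebo-only paired: 2 × √(0.8/28) = 0.34
- mixed model: 2 × √(0.4 × 1.8/28) = 0.32

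| Assumed r | As written | Placebo-only paired | Mixed model |
| --- | --- | --- | --- |
| 0.3 | 0.41 | 0.45 | 0.41 |
| 0.5 | 0.38 | 0.38 | 0.35 |
| 0.6 | 0.36 | 0.34 | 0.32 |
| 0.7 | 0.34 | 0.29 | 0.28 |
| 0.9 | 0.29 | 0.17 | 0.17 |

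The as-written contrast is less precise than pairing only when r exceeds 0.5. The mixed model is at least as precise as either throughout.

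**4. Regression to the mean.** Suppose subjects enter on one value above 8.0 from a normal distribution with mean m. Put c = (8.0 − m)/SD and L = φ(c)/(1 − Φ(c)).
- From the qualifying value to a later value, the expected fall is SD × (1 − r) × L. With m = 8.5, SD = 2, r = 0.6: c = −0.25, L = 0.3867/0.5987 = 0.646, fall = 2 × 0.4 × 0.646 = 0.52. With m = 9.0, SD = 1.5, r = 0.9: L = 0.427, fall = 1.5 × 0.1 × 0.427 = 0.06. All these inputs are assumptions.
- Between two later time points, the expected fall is SD × L × (r₁ − r₂), where r₁ and r₂ are their correlations with the qualifying value. If the correlation is constant, this is zero across months -3 to +9. If it decays, say from 0.8 to 0.6 with m = 8.5 and SD = 2, it is 2 × 0.646 × 0.2 = 0.26.

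**5. When does treat-to-target start?** The Summary of Procedure and the Protocol subsection under Methods and assessments say that it begins only at the end of the run-in. Table 1 marks its implementation at Visits I and II, and the risk section (Section 8) says that it is initiated during the run-in.

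**The case against.** The best case for the plan has four parts.

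- **The month -3 value is intended.** The sample size section says that all outcomes are measured at the beginning of the trial and then three-monthly. Section 6 calls quarterly HbA1c standard of care, and the investigators have access to laboratory results in the record. This shows intent, and the contrast from month 0 onward is fully scheduled. It would be too strong to infer that H1D cannot be computed at all. What stands is that no visit draws the sample, and that the protocol does not say which clinical value, by which method, would be used.
- **Mixing arms does not bias the estimate.** A reader might infer that a chance imbalance at month 0 distorts the result. Randomization follows the run-in, so all randomized patients share one expected baseline. The chance gap between the all-patient and placebo means (SD 0.5 × 2 × √(2/28) = 0.27) is already inside the as-written SE of 0.36 and is not a second error. Using only placebo after month 0 also sensibly keeps metformin out of the contrast.
- **Regression to the mean is not built into H1D.** A reader might apply the fall of 0.06 to 0.52 points directly to H1D. That fall runs from the qualifying value, which is not one of H1D's time points.
- **Contact and comparator.** The calls help to set titration doses, and Section 6 treats dedicated follow-up as what distinguishes the regimen, so contact is arguably part of it. The run-in change also gives patients a comparator of their own. Neither replaces a concurrent group on standard insulin.

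**Conclusion.** The point holds as a should-fix on a secondary aim. The firm parts are the unscheduled month -3 HbA1c, the unmatched before and after sets in a within-subject ANOVA, and a hypothesis worded beyond what an uncontrolled change can show.

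The arm mismatch adds no expected bias. Its precision cost is small at moderate correlation (0.36 against 0.34 at r = 0.6), nil at 0.5 and large only at high correlation (0.29 against 0.17 at 0.9). These figures rest on the protocol's SD of 2, 28 evaluable subjects per arm, assumed correlations, and reading all patients as all randomized patients.

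Regression to the mean matters chiefly if the eligibility value stands in for month -3, or if within-subject correlation decays with time. A reader might conclude that the analysis should be cut down to placebo subjects. The calculation does not support that, because the mixed model using every baseline is at least as precise (0.32 against 0.34 at r = 0.6). The randomized primary comparison is unaffected.

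**What to change.** 1. Add HbA1c, by the same HPLC method, to the Visit I draw in Table 1 and in both descriptions of the screening tests. State that the eligibility value will not be substituted.
2. Replace the repeated-measures ANOVA for H1D with a likelihood-based mixed model with within-subject correlation. Use months -3 and 0 from all randomized patients and months +3, +6 and +9 from the placebo arm. Contrast the change after month 0 with the change from -3 to 0.
3. Reword H1D as a descriptive within-subject change in patients on treat-to-target plus placebo, and drop the claim of better care for all patients.
4. Reconcile the passages that disagree on whether treat-to-target starts during or after the run-in, because H1D needs a before period that is clearly defined.

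The cost is one more HbA1c assay per subject at a visit where blood is already drawn, some analysis wording, and a weaker stated conclusion. Item 1 is the urgent one, since a sample missed at Visit I cannot be taken later.
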